### Exploratory End Point

Exploratory end points will further evaluate a broader range of clinical, operational, alarm-related, and user experience outcomes. Time-to-event clinical end points include time from T_0_ to initiation of key treatments, such as antibiotics, IV fluids, vasopressors, oxygen, or advanced respiratory support. Additional timing end points include the interval from T_0_ to RRT activation and from T_0_ to unplanned transfer to an HDU or ICU. Resource use outcomes will be explored, including length of hospital stay, rates of admission to higher-level care, frequency of RRT activation, and in-hospital mortality.

Analysis of alarms will include identifying the frequency, type, and clinical relevance of alerts triggered by the continuous vital sign monitor, as well as the proportion of alarms that are associated with escalation events. Patient and health care staff experience will be evaluated via structured questionnaires and semistructured interviews.

### Health Care Staff Questionnaire and Interview

An adapted System Usability Scale questionnaire will be used to evaluate health care staff experiences with the Portrait Mobile system (Figure S2 in Multimedia Appendix 1). This adaptation is based on a validated framework designed to quantify user experience and acceptance [30]. Consent will be obtained before staff participation, and the questionnaire will be completed online on an electronic form via Greenlight Guru [31]. Responses will be captured using a 5-point Likert scale ranging from “strongly agree” to “strongly disagree,” allowing for precise measurement of attitudes toward regular use, complexity, integration of functions, and overall usability. Open-ended questions at the end will permit staff to share any specific experiences or suggestions for improvement, enhancing qualitative understanding of the quantitative findings.

Semistructured interviews will be conducted using a predefined guide of questions formulated following a literature review (Figure S3 in Multimedia Appendix 1). The guiding questions follow themes regarding system functionality, patient safety implications, effectiveness, adequacy in training, practical barriers and facilitators, technological challenges, and suggestions for system enhancements. These interviews will be audio recorded, anonymized, and transcribed verbatim, followed by analysis using NVivo (version 12; Lumivero) [32].

### Patient Questionnaire and Interview

At least 24 hours after being recruited to the trial, patients will complete a questionnaire to assess their perceptions and experiences of the Portrait Mobile system (Figure S4 in Multimedia Appendix 1). This aims to collect information on comfort, usability, perceived impact on health care outcomes, and overall satisfaction with the monitoring device.

Additionally, a follow-up telephone interview will be conducted approximately 2 weeks after discharge to evaluate longer-term perceptions and outcomes (Figure S5 in Multimedia Appendix 1). These interviews are structured to capture detailed information on patient experiences and suggested improvements.

### Statistical Analysis

#### Primary End Point Analysis

Among the 2 groups (blinded and unblinded), the primary comparison will be the time from device-defined deterioration to objective escalation. The primary analysis will be performed in the population of patients who experience at least one device-defined deterioration episode, restricted to only 1 episode per patient (the first). Time-to-event methods will be used, with Kaplan-Meier curves constructed for each arm to visualize the distribution of time to escalation. The primary hypothesis test will use a log-rank test comparing the survival curves between arms, and a Cox proportional hazard model will be fitted with the interventional arm as the main exposure to estimate the hazard ratio for escalation (intervention vs control) with corresponding 95% CIs. The Cox model will be adjusted for key baseline covariates (age, sex, and comorbidity burden [Charlson Comorbidity Index]).

Patients with a device-identified deterioration without an escalation event during follow-up until their censor time will be treated as right censored in all time-to-event analyses. Proportional hazard assumptions will be evaluated using standard diagnostics such as Schoenfeld residuals. If these assumptions are materially violated, alternative or supplementary summaries such as restricted mean time to escalation up to a predefined time horizon may be reported in sensitivity analyses.

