## Methods

### Study Design

A prospective, interventional randomized controlled trial will be conducted using a mixed methods approach. It is an open-label, 2-arm study that aims to recruit 200 patients over a 1-year period. Patients will be randomized using an online tool (Greenlight Guru Clinical) on a 1:1 basis into an alerting and nonalerting group ( Figure S1 in Multimedia Appendix 1). This study will be conducted on 2 postsurgical wards at the West Middlesex University Hospital, London, with a capacity of 64 beds, providing orthopedic, general surgical, urological, gastroenterological, and gynecological care.

Patients are screened after the morning ward round, and those who are expected to remain in hospital for at least 1 night are approached by the research team for consent and assessment against the inclusion and exclusion criteria. Most of these patients are postoperative, although a small number are preoperative. All patients will be fitted with a continuous vital sign monitor (Portrait Mobile; GE HealthCare) from recruitment until either discharge from hospital or transfer to another unit. This CE-marked device (European Union certificate CR-03-1004-804-22) consists of 2 wearable sensors: a wrist-mounted saturation probe measuring both the oxygen saturation and pulse rate and a chest sensor measuring the respiratory rate. Both groups will have vital signs monitored as per the standard of care, intermittently acquired every 4 to 6 hours by health care staff using the National Early Warning Score 2 for identification and escalation of a deteriorating patient [19].

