Only the alerting group will have their continuous vital signs transmitted to a visible central viewer dashboard located at the nursing station and have audible alarms enabled on both the bedside hub monitor and the central viewer. All ward health care staff have access to real-time patient data and alarms; however, the nurse in charge is responsible for recognizing alarms, logging them, and informing the bedside nurse to respond appropriately. The intervention in this trial is the activation of real-time alerting through the continuous vital sign monitor, and alarms are managed entirely by the usual ward clinical team. They follow standard hospital escalation protocols, escalating deteriorating patients to the ward physician during daytime hours, the on-call physician out of hours, or the critical care outreach team. The critical care outreach team (also known as the rapid response team [RRT]) is an existing hospital team of specialized nurses who respond to acutely unwell patients requiring urgent assessment or intervention outside of the ICU. In the nonalerting group, health care staff are blinded to the continuous monitoring data.

To address alarm fatigue, several considerations have been taken. The alerting thresholds and announcement delays were derived from the Continuous Vital Sign Monitoring in Surgical Wards (COSMOS) pilot study, which conducted its initial phase by analyzing alarm data (pulse rate of <45 beats per minute [bpm] or >130 bpm sustained for ≥30 seconds, respiratory rate of <4 breaths per minute sustained for ≥30 seconds or >30 breaths per minute sustained for ≥120 seconds, apnea sustained for ≥30 seconds, and peripheral oxygen saturation of <85% sustained for ≥90 seconds or <80% without delay) [20]. These clinically validated alarm thresholds and built-in delay minimize false alerts caused by artifacts or transiently deranged vital signs. The central viewer is stationed at the nursing bay, beside the desk of the nurse in charge, who triages alarms. In addition, all ward staff received structured device training from GE HealthCare representatives focusing on correct interpretation, prioritization, and escalation of alarms.

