### Sample Size

In a pilot study, approximately 15% of patients wearing the continuous vital sign monitor generated at least one physiological alarm, with an average response time of 154 minutes [21]. In this trial, we defined a clinically meaningful target as a reduction in response time from 154 minutes to 60 minutes, corresponding to an estimated hazard ratio of 2.6 for time to response between the alerting and nonalerting groups. Therefore, recruiting a minimum of 200 patients, 100 in each arm, yields at least 30 participants with analyzable alert events. This is sufficient in providing reasonable precision for estimating the primary effect size and to support analyses of secondary outcomes.

In a previous feasibility study, 969 respiratory rate alerts were generated from 276 patients, supporting the assumption that a sample size of 200 patients generates sufficient signal volume for detailed alarm analyses [21].

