### Strengths and Limitations

The strengths of the WARD-AMS study include the randomized design and prospective real-world deployment in an active general surgical ward. The study is being conducted in 2 separate wards, which captures variability in management and staff practices. In addition, both quantitative and qualitative data will be analyzed.

The limitations include the study being conducted in a single center with established escalation pathways. However, these are representative of a typical National Health Service surgical ward, which uses the National Early Warning Score 2 as a track-and-trigger threshold system supported by critical care outreach nurses, and therefore, the results are transferable to similar settings. Lack of blinding of clinicians in the alerting arm may introduce the possibility of performance and detection bias. However, as continuous vital sign monitoring is intended to modify clinical response behavior, staff awareness will reflect real-world practice in assessing implementation and effectiveness.

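### Ward is left out of the Cox model for a staff-response end point, although the plan expects practice to vary between its two wards; this may pull the hazard ratio toward 1 and cost some power

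*Protocol article*

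**What the plan says.** Under Primary End Point Analysis, the protocol article names an unstratified test: "The primary hypothesis test will use a log-rank test comparing the survival curves between arms". A Cox model then supplies the hazard ratio and 95% CI, and its covariates are listed: "The Cox model will be adjusted for key baseline covariates (age, sex, and comorbidity burden [Charlson Comorbidity Index". Ward appears in neither.

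Other sections bear on whether ward matters:

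- Study Design: "This study will be conducted on 2 postsurgical wards at the West Middlesex University Hospital, London, with a capacity of 64 beds".
- Study Design, on who handles alarms: "the nurse in charge is responsible for recognizing alarms, logging them, and informing the bedside nurse to respond appropriately".
- Definition of T_Action: the end point is the earliest of a rapid response call, an unplanned transfer, a new high-acuity treatment order, or alarm acknowledgment on the nursing log. All of these are staff actions.
- Strengths and Limitations: "The study is being conducted in 2 separate wards, which captures variability in management and staff practices".
- Study Design, on allocation: "Patients will be randomized using an online tool (Greenlight Guru Clinical) on a 1:1 basis into an alerting and nonalerting group". No stratification by ward is mentioned.

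**The concern.** The plan measures staff behaviour and names the ward as a place where staff behaviour varies. It then adjusts only for characteristics of the patient. Ward is known at baseline for every patient and is a natural candidate to explain response time.

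In a Cox model, leaving out a factor that affects the outcome shrinks the treatment hazard ratio toward 1, even when that factor is balanced between arms. With only about 30 patients expected in the primary analysis, there is little power to spare. The stake is an understated effect and a somewhat greater chance of an inconclusive confidence interval.

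**Working it through.** **The plan's own figures.** Sample Size reports that "approximately 15% of patients wearing the continuous vital sign monitor generated at least one physiological alarm, with an average response time of 154 minutes" and sets as its target "a reduction in response time from 154 minutes to 60 minutes".

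- Analyzable patients: 200 × 0.15 = 30, as stated.
- Hazard ratio with exponential times: 154 / 60 = 2.57, rounded to 2.6, as stated.

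**Reference power.** The article states neither alpha nor power, so two-sided alpha 0.05 is assumed. By Schoenfeld's formula with 30 events and equal arms, z = √(30/4) × ln 2.6 − 1.96 = 2.739 × 0.956 − 1.96 = 0.66, which gives power of about 0.74. For 80% power, 35 events are needed by Schoenfeld's formula, or 40 by Freedman's.

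**Effect of ward.** The documents give no ward effect, so a range was simulated. Assumptions: 30 patients, 15 per arm, all with an event, exponential times, arm hazard ratio 2.6 and wards split about equally. The ward hazard ratio runs from 1 (no difference) to 4.

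Cox model, arm only against arm plus ward (4,000 runs each):

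| Ward HR | Mean log HR without / with ward | Mean SE without / with | Power without / with |
|---|---|---|---|
| 1 | 1.00 / 1.03 | 0.43 / 0.44 | 0.67 / 0.66 |
| 1.5 | 0.98 / 1.03 | 0.42 / 0.44 | 0.65 / 0.67 |
| 2 | 0.94 / 1.04 | 0.42 / 0.44 | 0.62 / 0.67 |
| 3 | 0.84 / 1.02 | 0.41 / 0.44 | 0.54 / 0.65 |
| 4 | 0.78 / 1.03 | 0.41 / 0.44 | 0.48 / 0.65 |

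The standard error is slightly smaller without ward. The loss comes from the shrinking estimate. At a ward hazard ratio of 3, the mean log HR of 0.84 without ward corresponds to a hazard ratio of e^0.84 = 2.3, against e^1.02 = 2.8 with ward. The true log HR is ln 2.6 = 0.96; the with-ward figures lie a little above it because of small-sample bias, so the comparison to read is without against with ward.

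With the plan's three patient covariates also in the model, power without and with ward is 0.65 and 0.64 at ward HR 1, 0.61 and 0.66 at 2, and 0.54 and 0.64 at 3. The change is therefore −1, +5 and +10 points.

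**Would stratifying the log-rank test do the same?** Power of the unstratified and ward-stratified log-rank tests (10,000 runs each):

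| Ward HR | Unstratified | Ward-stratified | Change (points) |
|---|---|---|---|
| 1 | 0.69 | 0.63 | −6 |
| 1.5 | 0.67 | 0.63 | −3 |
| 2 | 0.63 | 0.64 | +1 |
| 3 | 0.55 | 0.64 | +10 |
| 4 | 0.50 | 0.65 | +15 |

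(Changes are computed before rounding.) Stratifying splits 30 patients into two sets of about 15 and compares arms only within each. That costs information which one extra covariate does not.

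**Validity.** With no treatment effect, both log-rank versions reject in about 6% of trials at every ward hazard ratio. The small excess over 5% is already there when the wards do not differ, so ward is not its cause.

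**Model size.** Arm plus age, sex and Charlson index, each as one term, is four terms: 30 / 4 = 7.5 events per term. Adding ward makes five: 30 / 5 = 6. Arm plus ward alone gives 30 / 2 = 15.

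**The case against.** The best defence is that nothing here is invalid. Patients are individually randomized, no ward stratum is stated that the analysis would have to mirror, and the unstratified log-rank test is a legitimate choice. All of that stands.

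The size of any harm is also unknown. The article mentions ward variability only in words, as a strength of the design, and gives no response times by ward. Much of the setting is shared: one hospital, the same escalation protocols and outreach team, National Early Warning Score 2, and common device training. The wards may differ by much less than 2-fold, in which case little is lost. This also stands, and it is why the result is given as a range.

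It could be said that a ward-adjusted analysis belongs in a statistical analysis plan that is not shown. A fuller plan could add one, but this article states its covariate list outright rather than leaving it open, so it is fair to comment on the list.

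Three stronger readings are tempting, and the documents support none of them:

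- That omitting ward biases the comparison or loses precision in the sense of a wider interval. The simulation shows neither; the mechanism is attenuation.
- That the plan contradicts itself. Noting that two wards capture variability does not conflict with an unstratified test.
- That the remedy is to stratify the primary test by ward. Below about a 2-fold ward difference, that would lower power.

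That the unadjusted log-rank p-value and the adjusted Cox interval can disagree is true of many plans. It is a separate matter from ward.

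**Conclusion.** The point holds as a minor improvement. The plan adjusts a staff-response end point for patient traits only and leaves out the one factor that it names as a source of variation in staff practice. The test remains valid.

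With about 30 events and a true hazard ratio of 2.6, including ward as a Cox covariate changes power by about −1 point if the wards do not differ, +5 at a 2-fold difference and +10 at a 3-fold difference. These figures describe the Cox estimate and whether its 95% CI excludes 1. The power of the unstratified log-rank test is unaffected by a change to the Cox model.

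The figures rest on two-sided alpha 0.05, no censoring, an even ward split and an assumed ward effect. Censoring would lower all the power figures.

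**What to change.** Before outcomes by arm are seen, prespecify ward as a covariate, not a stratum, in the Cox model that supplies the hazard ratio and its 95% CI. Keep the other covariates few at about 30 events, for example by reporting the fuller model with age, sex and Charlson index as a sensitivity analysis. Leave the log-rank test unstratified.

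The article's abstract says that analysis is under way, while its Results section places analysis after data collection ends. If outcomes by arm have already been examined, report the ward-adjusted model as a post hoc sensitivity analysis and label it so.

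The change needs a sentence or two in the analysis plan and no new data beyond each patient's ward. The downside is one more model term at a low event count, and about 1 point of power if the wards turn out alike.

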#### Exploratory Analysis

Analysis of all clinical end points involving time-to-event data will be conducted using survival analysis methods, specifically Kaplan-Meier curves and log-rank tests to assess differences between the alerting and nonalerting arms.

Length of hospital stay will undergo additional analysis using nonparametric tests to evaluate differences in median length of stay between the 2 study arms. Secondary outcomes presented as categorical variables, such as frequency of HDU or ICU admission and RRT activation, will be compared using chi-square tests. These will be conducted using RStudio (Posit PBC) [33].

Quantitative data from both the health care staff and patient questionnaires will be analyzed to illustrate frequency distributions and central tendencies regarding system usability, satisfaction, and other outcome measures. Likert-scale responses will be numerically scored and statistically analyzed using RStudio [33].

Interview transcripts will be analyzed by generating a set of codes that will be predefined from existing literature and serve as initial labels to index relevant data segments. This will be refined through iterative coding and thematic consolidation to ensure accurate and meaningful categorization by merging similar codes and splitting overly broad codes. To enhance validity, this method will be performed by 2 independent researchers until thematic consensus and data saturation are reached.

The quantitative outcomes (time to acknowledgment of deterioration, time to treatment initiation, escalation of care, and alarm analyses) will be compared with qualitative themes from the staff and patient questionnaires and interviews using a triangulation approach for a better understanding of the effect and implementation of continuous vital sign monitoring. A joint display table will be developed aligning key quantitative results with corresponding qualitative findings, identifying areas of convergence, complementarity, or divergence.

This integrated mixed methods approach aims to facilitate a comprehensive understanding of the usability, acceptability, and practical implications of the Portrait Mobile system.

### Data Governance and Management

The study data will be extracted by a staff member employed as a business intelligence research analyst at Chelsea and Westminster Hospital National Health Service Foundation Trust. These data are stored on secure trust servers, with access restricted to the core study team. These data will be retained for 15 years in accordance with trust policy. An audit trail is available in the EPR.

Each participant will be assigned a unique trial ID during randomization. Variables extracted will include demographics (eg, date of birth, sex, and ethnicity), medical and medication history, vital signs, blood tests, transfer of care, and length of stay. Missing data will not be imputed and will be analyzed as available.

## Results

This manuscript reports the approved study protocol for the WARD-AMS trial, which received favorable ethics approval in April 2024. A total of 200 patients meeting the inclusion and exclusion criteria were successfully randomized, recruited, and completed the period of continuous vital signs monitoring. All patients completed the baseline questionnaire; as of December 2025, a total of 92 patients have participated in the telephone interview. In addition, 50 staff members completed the questionnaire, of whom 27 consented to participate in the interview. As of December 2025, 10 staff members have been interviewed. All data collection is projected to be completed by February 2026; thereafter, it will be cleaned, interviews transcribed, and prepared for data analysis. Results will be finalized with a manuscript submitted for publication by mid-2026.

## Discussion

### Expected Findings

The WARD-AMS study is expected to demonstrate that continuous vital sign monitoring of postoperative patients in a general surgical ward reduces the time from device-defined physiological deterioration to the first objective escalation event (acknowledgment or clinical action) compared to standard-of-care intermittent monitoring. Quantitative analysis will evaluate the changes in response latency, time to treatment, and escalation of care. Qualitative analysis will focus on contextualizing these outcomes by exploring staff and patient experiences. Together, these findings will clarify how continuous vital sign monitoring influences patient outcomes to understand better how to implement these technologies into existing clinical workflows.

### Comparison With Prior Work

Previous observational and before-and-after studies have set a foundation to build on. These study designs and systematic reviews are limited by heterogeneity in device and sensor technologies, alerting protocols, escalation pathways, and staff engagement practices [12,13,34,35]. The COSMOS pilot prospective study evaluated alerting parameters; however, it was not powered for achieving statistical significance [20]. Our study allows for a more comprehensive assessment of the clinical benefit and implementation feasibility in a real-world setting.

